**Figure 2 F2:**
[figure not shown]
The implementation research logic model. DR, diabetic retinopathy; FHC, family health centres.

### Outcomes

Prespecified outcomes of the effectiveness of the DR pathway and the evaluation of the implementation strategy are tabulated in tables 2 and 3, respectively.

**Table 2 T2:** DR pathway (intervention)-related outcomes

Outcomes	Indicators	Source of data
Clinical effectiveness	Proportion of people screened for DR in each family health centres over 12 months. Proportion of referred patients with STDR. Proportion of ungradable retinal images and percentage of cataract identified from referring these patients. Risk and complication burden in people screened for DR Presenting visual acuity of those referred from the DR pathway compared with those who self-referred to secondary care. Generalisability of the prevalence data compared with house-to-house survey in a neighbouring district.	Data from monthly entries into EHR and study database. −
Safety	Data on complications of the DR pathway	EHR and study database
Cost-effectiveness	The key outcome is the number of cases of severe visual impairment or blindness due to STDR averted as a result of the new DR care pathway and resultant QALY gain. Estimated QALY gain from laser treatment of STDR and from cataract surgery, using utility values from Rachapelle *et al*.^32^ Assumption that the effect of no screening is as in historic studies that reported the rate at which STDR leads to blindness if left untreated.	Data collected in the study, data from the literature and expert opinion where data could not be collected.
Efficiency	Efficiency is defined as optimal use of the service. For this purpose, we will first estimate the time required to process one patient from the path-process analysis. This estimate will be used to determine the number of patients who can be seen on a day. We will then calculate (1−number of patients screened)/number of patients who can be screened). Proportion can be used in a p-type control chart.^33^	Capture efficiencies in structures, resources and processes across the DR care pathway from staff interviews. Path-process mining of patients screened in family health centres analysis will be based on detailed time-event logs of approximately 70 patients from the 16 FHCs
Patient satisfaction	Patients willingness to be screened and their satisfaction with the information provided to them and the care they received	Patient interviews and telephone survey of patients referred to secondary care for treatment
Timeliness	Path-process mapping at family health centres to understand delays in pathway Reasons for non-attendance for those referred to secondary care for treatment of STDR	Path-process mapping at family health centres to understand delays in DR care pathway Patient survey and secondary care records
Equity	Age and gender-based prevalence of DR and STDR will be reported on consented patients from all family health centres. Reasons of non-referral of patients that require referrals will be recorded. Numbers denied screening despite willingness to be screened will also be reported.	Data from EHR and study database.

DR, diabetic retinopathy; EHR, electronic health records; FHCs, family health centres; QALY, quality-adjusted life year; STDR, sight-threatening diabetic retinopathy.

**Table 3 T3:** Outcomes of the evaluation of the implementation strategy

Outcomes	Indicators	Assessment and data source
Acceptability	Willingness of each family health centres to be involved in the DR care pathway. Staff willingness to train patients acceptability of the pathway.	*Assessment:* Readiness to implement the DR care pathway in the 16 family health centres and any reasons for delay. *Data source:* Clinical performance from family health centres that will include monthly uptake of DR screening at each centre and any reports on barriers causing delays in implementation provided by the project manager. *Assessment:* Proportions of trained ASHAs, nurses and doctors per family health centres, increase in doctors trained in laser surgery in secondary care, proportions willing to be included in train the trainer programme. The denominator will be total numbers of each personnel available to be trained on the date of implementation. *Data sources:* Accreditation and certification records; structured interviews of at least 5 nurses and 5 primary care doctors from 16 family health centres, 3–5 ophthalmologists from secondary and tertiary care, 2 data entry operators and 5 ASHAs and 1 health service administrator to understand challenges for acceptance. *Assessment:* Screening attendances per family health centres over 12 months. *Data sources:* Clinical performance data and a telephone questionnaire survey for screened and referred patients to evaluate reasons for attendance and non-attendance.
Adoption	Uptake of DR care pathway at primary, secondary and tertiary care. Uptake of training by staff. Uptake of screening programme by patients. Adoption of DR care pathway by the Government of Kerala for state-wide implementation.	*Assessment:* Proportion of staff at primary, secondary and tertiary care willing to integrate DR care pathway in their workload. *Data source:* Family health centres data and staff interviews. *Assessment:* Demand training sessions; attendance rates at training sessions. *Data source:* Number of training sessions and attendance registers at training sessions. *Assessment:* Increase in proportions of patient screened over 12 months. *Data source:* EHR and study database. *Assessment:* A policy paper by the Government of Kerala for state-wide adoption of the DR care pathway as part of diabetes care for all patients. *Data source:* A detailed scale-up plan will be developed for each district based on the clinical and cost-effectiveness data from this study to inform policy.
Appropriateness	Appropriateness of family health centres for DR screening. Appropriateness of the complex DR care pathway across primary and secondary care. Appropriateness of referrals to secondary care.	*Assessment:* Qualitative data on barriers and facilitators of the delivery of screening and treatment in secondary care. *Data sources:* Interview of staff at family health centres and secondary care, patient telephone survey on pathway from FHCs to secondary care. *Assessment:* False positive referrals from data collection at secondary care. *Data sources:* Study database; data from patient telephone survey.
Cost	Costs to the Government of Kerala and societal costs of the DR screening programme and subsequent treatment.	*Assessment:* Costs of the DR screening and treatment costs in total and per person, including the costs of staff training and cameras (suitably annuitised), staff costs and travel costs of patients. *Data sources:* Data collected in the study baseline and data from other services in India and from the literature.
Feasibility	Screening rate per family health centres. Barriers to monthly screening uptake.	*Assessment:* Monthly increase in numbers of FHCs added to the programme. *Data source:*Interview and monthly report from project manager on facilitators and barriers on each part of the pathway.
Fidelity	Degree of the DR care pathway implementation. Validation of the DR grading within the telemedicine pathway. Delivery of training and the impact on the DR care pathway.	*Assessment:* Fidelity evaluation in 16 family health centres using a path-process analysis of the screening to identify the common screening pathway across centres. *Data source:* The path-process analysis will be based on detailed time-event logs of 70 patients from the 16 family health centres; a telephone follow-up of referred patients to evaluate uptake of referrals. *Assessment:* Validation of the DR grading will be assessed by the agreement of the DR grade reported by the optometrists at the reading centre in the tertiary centre and those reported by the ophthalmologists in the secondary care centres. *Data sources:* DR grading of referred patients obtained from the reading centre vs secondary care. *Assessment:* Increase in numbers of trained staff per month. *Data sources:* Staff interviews, structured observations and review of facility records. The proportions of doctors trained on laser delivery; data quality on the database; increase in non-communicable diseases registration following start of programme due to training of ASHA workers on diabetes and DR; increase in numbers of patients treated for STDR following training.
Penetration	Increase patient awareness of diabetes and DR and uptake of the DR screening pathway in patients with diabetes.	*Assessment:* Increase uptake of DR screening by patients registered in non-communicable diseases registers. *Data sources:* from non-communicable diseases register and EHR.
Sustainability	Policy makers to prepare policy on up-scale and sustainability plan for DR pathway. Integration of DR pathway in weekly activities in FHCs	*Assessment:* Availability of a policy paper from Government of Kerala on state-wide scale up of the DR care pathway. This will be considered a success of the programme. *Data sources:* Scale up plan for other districts including plan to purchase retinal cameras and acceptance of guidelines and training material for state-wide roll out. *Assessment:* Integration of DR pathway in EHR. *Data source:* EHR records of DR screening as part of non-communicable diseases care pathway.

ASHA, accredited social health activists; DR, diabetic retinopathy; EHR, electronic health records; FHCs, family health centres; STDR, sight-threatening diabetic retinopathy.

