### Description of the standard of care

Currently, patients with diabetes are not systematically screened for DR in the public health system. Most patients present to the tertiary centre voluntarily either because of increased awareness of complications of diabetes or due to visual impairment. Therefore, the current standard of care will be captured as the number of patients presenting to the tertiary centre for an eye consultation for DR over a period of time as there is no baseline data in the primary and secondary care. This cross-sectional survey of the patients presenting at the FHCs will provide information on the uptake of screening of people registered in the non-communicable diseases register at the start of the study. The prevalence of DR and STDR of the screened population will be estimated from the numbers screened in all the non-communicable diseases registers during this period.

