### Sample size

We have chosen the proportion of patients in the non-communicable diseases register with diabetes screened for DR as our primary outcome variable.

Justification of the choice of primary outcome: this variable captures the effectiveness of our intervention as well as the fidelity of implementation. Other facts that informed our choice of the primary outcome is that we expect a short implementation time of 7–9 months during which other outcomes such as number of patients treated may not be a feasible option. Therefore, we have estimated the sample size based on this primary outcome.

Our calculations are complicated by the expected increase in number of people with diabetes in the non-communicable diseases register as public awareness of diabetes and DR increases so the denominator of numbers screened will be the number of people registered in the non-communicable diseases in each FHCs at the start of the cross-sectional study. There is no data on the baseline proportion of patients that attend the tertiary centre for screening. The prevalence of diabetes is between 10% and 16% in Thiruvananthapuram of which 8% are estimated to have DR and 3% to have STDR but about 20% may have to be referred. Assuming a finite population of 40 000 patients with diabetes, a simple random sample of 377 patients will be needed. However, we expect large design effects due to clustering patients within FHCs. There is not enough data to calculate the value of this design effect and therefore we assume it to be 3 to give a final sample size of 1131, which is equivalent to assuming a within-FHCs intracluster correlation coefficient of approximately 0.03 (n=16 FHCs) with negligible residual clustering by the intermediate cluster level of ASHAs, where mean cluster size is smaller.

As described by Becker *et al* in mammography screening,^28^ we expect sources of bias in the implementation programme that will likely influence the sample size calculation. Unscreened DR cases that already exist in the community may contribute to an over-estimation of the effect of screening. We expect lead-time bias because of our short implementation period and so some DR in the community may be missed. A comparison of numbers with DR in FHCs with longer implementation period with those of shorter period may adjust for this bias. We intend to provide a descriptive analysis as well as a temporal comparison using time series analysis.

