## Discussion

At the conclusion of this study, we hope to assess the effectiveness and implementation outcomes of a complex DR care pathway integrating care at primary, secondary and tertiary care, covering a proportion of the diabetic population in Thiruvananthapuram. The study will set the scene for a policy for State-wide Screening and Treatment Pathway for Diabetes. Early identification of STDR and other complications due to this holistic approach and timely treatment are expected to have a positive impact on rates of blindness, chronic kidney disease, cardiovascular complications and thereby improve health, reduce multimorbidity and mortality. A DR pathway that straddles primary, secondary and tertiary levels of care, leveraging technology may have advantages of cost effectiveness and ease of implementation in LMICs compared with the current practice of detection and management of self-reported cases in tertiary centres.

This study outlines how the effectiveness of a DR care pathway and its implementation will be evaluated.^21 22^ This study is timely given the increasing numbers of people with diabetes and pressure on finances available for healthcare, necessitating task shifting to enable better coverage of the population. The study will also examine the organisation functions such as structure, resources and processes that would contribute to better outcomes. We will also examine whether this additional task is feasible given the current skill levels and workload of FHCs and secondary hospitals. The study will reveal whether current health seeking behaviour of patients will support screening, especially when an invasive procedure is requested when there is no obvious impact on quality of life of the patient. By addressing a key gap in knowledge due to lack of research in this area, we will be able to decipher the barriers and facilitators that influence the successful implementation of such a programme in the public system in India. The results of this study may inform the adoption of this pathway in other areas in India and globally. However, the complexity and number of implementation strategies, local contextual factors and lack of validated implementation outcomes may limit generalisability of the results and implementation of this pathway elsewhere.

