There are limitations, however, to the study design. We do not have baseline data on DR screening in the study location as these screening programmes are non-existent. For this reason, we are examining the effectiveness of the pathway in terms of presenting visual acuity for referable cases as ‘proximal’ outcomes. In addition, when there is no concurrent control group, causal inferences are difficult to make and may lead to both measured and unmeasured biases. When examining implementation, logistical issues, variations in healthcare facilities, socioeconomic variation and quality of healthcare personnel may likely affect our study. However, the study design avoids the ethical challenges of having a control group with no DR screening. Therefore, the study design is by necessity non-randomised and observational and will rely on newly trained staff members to collect data, which is likely to differ in completeness between the 16 FHCs. We expect an increase in referral rates after implementation of the intervention due to better public awareness, increasing knowledge of ASHAs and improved case ascertainment, at least in some FHCs. We will also examine the impact of cataract in the community and this has not been studied before in any other DR pathway. We have tried to minimise the limitations by the use of robust statistical techniques and the use of various data sources to elicit a greater understanding of how the programme will lead to better health outcomes.

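### The visual acuity comparison between all pathway referrals and self-referrals to secondary care mixes case mix and mode of detection with any pathway effect, and its comparator site conflicts with the described standard of care

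*Protocol article*

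**What the plan says.** Under Clinical effectiveness, Table 2 (Outcomes) lists several indicators. One is "Presenting visual acuity of those referred from the DR pathway compared with those who self-referred to secondary care". It names no diagnosis, DR grade or reason for referral for either group.

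The limitations paragraph of the Discussion explains its role. Because there are no baseline screening data, "we are examining the effectiveness of the pathway in terms of presenting visual acuity for referable cases as ‘proximal’ outcomes".

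Description of the standard of care says where people go now and why: "Most patients present to the tertiary centre voluntarily either because of increased awareness of complications of diabetes or due to visual impairment". It adds that "the current standard of care will be captured as the number of patients presenting to the tertiary centre", "as there is no baseline data in the primary and secondary care". The first paragraph of the Discussion again refers to "current practice of detection and management of self-reported cases in tertiary centres".

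Sample size gives the expected yield among people with diabetes: 8% with DR, and "3% to have STDR but about 20% may have to be referred". Table 2 and Data collection both show that patients with ungradable images, including those caused by cataract, are among those referred.

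**The concern.** The two groups are formed in different ways, and both ways bear on visual acuity.

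- **Pathway group.** These people are invited from a register whether or not they have symptoms. They are then referred for STDR or for other reasons such as an ungradable image. On the plan's own figures, most of them do not have STDR.
- **Self-referred group.** These people come of their own accord, some of them because they already see poorly. To that extent, poor acuity is a reason for being in the group.

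The two influences pull in opposite directions. Selection on visual impairment lowers acuity among self-referrers and flatters the pathway. Cataract among pathway referrals lowers acuity there and counts against the pathway. Neither shows whether STDR is found at an earlier stage, which is what an acuity comparison could usefully describe.

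The site is a second problem. The comparator comes from secondary care, although the protocol says most self-presenters go to the tertiary centre and that secondary care has no baseline data. Whoever self-refers to secondary care may not represent the current practice that the pathway is meant to improve on.

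This is the listed clinical-effectiveness indicator that sets pathway patients against non-pathway patients on a patient outcome. The protocol intends its effectiveness data to inform the scale-up plan (Table 3, Adoption).

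**Working it through.** **Inputs (Sample size):** DR 8%, STDR 3%, referral about 20%, final sample 1131. I take the three percentages to share one denominator, people with diabetes who are screened. The protocol gives no sample size for the acuity comparison. The 1131 belongs to the uptake outcome (377 × 3 = 1131, as stated) and is used here only as a scale.

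**Ceiling on the share of referrals with the target disease.** If every case is referred, share = prevalence / referral rate.

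- STDR: 0.03 / 0.20 = 0.15, so at least 85% of referrals do not have STDR.
- Any DR: 0.08 / 0.20 = 0.40, so at least 60% of referrals have no DR.

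**Per 1131 screened:**

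| Group | Calculation | Number |
|---|---|---|
| Referred | 1131 × 0.20 | about 226 |
| With STDR | 1131 × 0.03 | at most 34 |
| With any DR | 1131 × 0.08 | at most 90 |
| Referred without DR | 226 − 90 | at least 136 |

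**Sensitivity to the 20%.** The protocol words this rate loosely. For STDR to make up even half of referrals, the referral rate would have to fall to 0.03 / 0.50 = 6%.

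**What case mix alone could do.** This is an illustration, and its inputs are assumptions, not protocol figures. Let mean acuity be identical within each disease group in both arms, so that there is no pathway effect. Let people with and without the target disease differ by g = 0.3 logMAR. Let the target share be s among pathway referrals and c among self-referrals. The spurious difference is then (c − s) × g.

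| s | c = 0.50 | c = 0.80 | c = 1.00 |
|---|---|---|---|
| 0.15 (STDR ceiling) | 0.105 | 0.195 | 0.255 |
| 0.40 (any-DR ceiling) | 0.030 | 0.120 | 0.180 |

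The sign depends on whether people without the target disease see better or worse than those with it. The documents do not settle that. Selection on visual impairment would come on top and is not in the table.

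**Site, set side by side.** Description of the standard of care: most present to the tertiary centre, and there are no baseline data in secondary care. Discussion, first paragraph: self-reported cases are managed in tertiary centres. Table 2: self-referred to secondary care. The first two agree with each other, and the third draws from elsewhere.

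**The case against.** **Role.** Acuity is not the main test of the pathway. The primary outcome is screening uptake, and Statistical analyses models only uptake and numbers referred for STDR. Acuity is one of several indicators, and the Discussion calls it proximal. This stands, and it limits the weight of the point.

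**Missing detail.** The article gives no analysis for this indicator, so restriction or adjustment may be in the full protocol or SAP. A reader might infer that an unadjusted difference is planned, but the documents do not say so. What the article does fix is which two groups are compared, and it defines them without any diagnostic limit.

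**Pathway case mix can be seen.** The reading centre records DR grade, cataract and gradability, and Table 2 reports referred STDR and ungradable images separately. That makes the fix easy on the pathway side. It does not describe the self-referred group.

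**Stronger readings.** A reader might infer that the comparator is a symptomatic group. The protocol gives increased awareness as a reason alongside visual impairment, with no split, so only partial selection on symptoms is supported. A reader might also infer that the groups have different diseases. The self-referrers' diagnoses are not defined and the groups may overlap, so only a difference in case mix is supported. Nor is cataract wholly off target, since Table 2 counts QALY gain from cataract surgery.

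**Intended contrast.** Finding disease before vision is lost is the purpose of screening, so better acuity among screened people is partly what is hoped for. That is true for people with STDR. It does not apply to the 85% or more of referrals without it.

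**Site.** The standard-of-care section describes the period before the pathway and says most, not all. Self-referral to secondary hospitals during the study is possible, because the project trains and equips them. The conflict therefore needs reconciling and is not a proven error. A tertiary comparator could bring its own severity selection, since Setting sends severe cases there.

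**General caveat.** The Discussion admits that causal inference is difficult without a concurrent control. That does not address this comparator, the mixed reasons for referral or the site.

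**Conclusion.** The point holds for one secondary effectiveness indicator. As defined, the comparison sets a referral group with at most 15% STDR (at most 40% any DR) against a self-referred group of undefined diagnosis that is partly selected on visual impairment. Case mix and mode of detection are mixed with any pathway effect, and the direction of the resulting bias is unknown. The comparator's site also disagrees with the protocol's own account of where self-presenters go.

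The ceilings rest on the Sample size figures sharing a denominator, on every case being referred, and on the approximate 20% being right. The logMAR illustration rests wholly on assumed inputs and shows only that a visible difference can arise with no effect. It would be wrong to conclude that the acuity result can carry no information on earlier detection, or that it undermines the primary outcome. The documents support neither.

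**What to change.** 1. Restrict the acuity comparison to ophthalmologist-confirmed STDR in both groups, and show the STDR severity distribution beside it.
2. Account for age and cataract where these are recorded.
3. Summarise acuity of ungradable and cataract referrals separately.
4. Report the result as descriptive stage at presentation, not as effectiveness, and align the Discussion sentence with this.
5. Reconcile the self-referral site between Table 2, Description of the standard of care and the first paragraph of the Discussion. Use tertiary-centre patients only if acuity and DR grade are already recorded there.

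**Cost.** Items 1 to 4 are mainly wording. For pathway referrals, secondary-care ophthalmologists' DR grades are already planned for the agreement analysis. For self-referrers, availability must be checked at whichever site is chosen. The standard-of-care section plans only a count at the tertiary centre, and the situational analysis of self-referred patients in Table 1 names no site, acuity or grade. Moving the comparator could therefore require new data collection. The comparison will be smaller (at most about 34 pathway patients with STDR per 1131 screened) and the claim weaker.

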### Implementation strategies

The implementation strategies of the new DR care pathway are categorised as shown in table 1 into plan, finance, education, infrastructure, quality improvement and policy contexts. These categories are developed based on the discrete Expert Recommendations for Implementing Change (ERIC) taxonomy.^20 21^ The logic model is shown in figure 2.

**Table 1 T1:** Implementation strategies

Categories of implementation strategies^21^	Discrete implementation strategy^20^	Specific actions
Plan	Conduct local needs assessment	The study team will conduct a situational analysis of data from self-referred patients.
	Assess for readiness and identify barriers and facilitators	Assess barriers that may impede implementation of the DR care pathway, and strengths that can be used in the implementation effort by interviewing key stakeholders that is, family health centres staff, ophthalmologists in secondary and tertiary care, health service employees and patients.
	Develop a formal implementation blueprint	The blueprint will be used to guide the implementation of the whole DR care pathway and will be updated with time.
	Tailor strategies	Regular collaborative meetings will be held to tailor the implementation strategies to address barriers and leverage facilitators that are identified during various steps in the implementation.
	Stage implementation scale up and integration	The implementation will be staggered with five family health centres starting as pilots to enable small changes before gradually moving to other 11 centres. Addition of more centres during the staggered phase will be considered as sign of acceptability and feasibility. Ensure integration of the DR care pathway into EHR. In the long term, the adoption of the DR care pathway across the state of Kerala will be considered as success.
	Build a coalition	Cultivate relationships with staff at family health centres and secondary care centres, data entry operators, EHR team, project manager and the Government of Kerala health service departmental staff in the implementation effort and create a learning system to incorporate practitioner feedback.
	Develop academic partnerships	Partner with UK academic institutions for the purposes of shared training and bringing research skills to the implementation of the pathway.

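### The economic comparator treats no screening as no treatment, although the protocol's own standard of care is self-presentation and management at the tertiary centre; blindness averted and STDR QALYs are overstated to the extent that self-presenters benefit.

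*Protocol article*

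**What the plan says.** The cost-effectiveness row of Table 2 (Outcomes) defines the result as follows: "The key outcome is the number of cases of severe visual impairment or blindness due to STDR averted as a result of the new DR" (that is, the new pathway), together with the QALY gain that follows. It then fixes the counterfactual, assuming that "the effect of no screening is as in historic studies that reported the rate at which STDR leads to blindness if left untreated". The row allows inputs from the study, the literature and, where data could not be collected, expert opinion.

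Elsewhere the article describes care without the pathway. Under Description of the standard of care: "Currently, patients with diabetes are not systematically screened for DR in the public health system". The same section goes on: "Most patients present to the tertiary centre voluntarily either because of increased awareness of complications of diabetes or due to visual impairment". It concludes that "the current standard of care will be captured as the number of patients presenting to the tertiary centre for an eye consultation for DR". The Discussion suggests that the pathway may have cost-effectiveness advantages "compared with the current practice of detection and management of self-reported cases in tertiary centres".

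Self-referred patients also appear in the study's own measurements. Table 1 plans a local needs assessment: "The study team will conduct a situational analysis of data from self-referred patients". The clinical effectiveness row of Table 2 lists "Presenting visual acuity of those referred from the DR pathway compared with those who self-referred to secondary care".

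**The concern.** The article recognises a group of patients who reach eye care without screening and are managed there. The economic assumption then gives everyone in the no-screening arm the untreated course of STDR. Any blindness that current care already prevents is thus credited to the pathway.

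The result will be used. The Adoption row of Table 3 bases a scale-up plan for each district on the study's clinical and cost-effectiveness data. A policy-maker needs to know what the pathway adds to present services, and a comparison with no care at all does not show that.

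**Working it through.** **Figure to reproduce.** The article gives no value for blindness averted, QALYs gained or cost per QALY, so there is none to reproduce. The check concerns direction and possible size.

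**Inputs**
- Comparator: untreated course of STDR (Table 2, cost-effectiveness row).
- Current care: voluntary presentation (Description of the standard of care) and management (Discussion) at the tertiary centre.
- s, the share of pathway-treated STDR patients who would otherwise have self-presented and been treated: not given. The Sample size section says there are no data on the baseline proportion attending the tertiary centre for screening. Varied here as an assumption.
- f, the benefit of treatment after self-presentation as a fraction of the benefit of screening-led treatment: not given. Some patients present only because vision is already impaired, so f may be well below 1. Varied as an assumption.

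**Effect.** Let r be the risk of blindness if untreated and e the relative reduction from screening-led treatment.
- Averted per treated patient against the untreated course: r·e.
- Averted by current care alone: s·f·r·e.
- Averted by the pathway over current care: r·e·(1 − s·f).
- Overstatement factor: r·e / [r·e·(1 − s·f)] = 1/(1 − s·f). Both r and e cancel.

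STDR QALYs are overstated by the same factor if they are proportional to cases averted.

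| s | f | 1 − s·f | True number per 100 counted as averted | Factor |
|---|---|---|---|---|
| 0.10 | 0.25 | 0.975 | 97.5 | 1.03 |
| 0.10 | 1 | 0.90 | 90 | 1.11 |
| 0.25 | 0.5 | 0.875 | 87.5 | 1.14 |
| 0.50 | 0.25 | 0.875 | 87.5 | 1.14 |
| 0.50 | 0.5 | 0.75 | 75 | 1.33 |
| 0.50 | 1 | 0.50 | 50 | 2.0 |

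The factor is exactly 1 only if s = 0 or f = 0.

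**Cost per QALY.** Let t be the current-care treatment cost per self-presenter divided by the pathway cost per treated STDR case. If the stated analysis leaves current-care costs out, corrected over stated cost per STDR QALY is (1 − s·t)/(1 − s·f). Two assumed cases with s = 0.30:
- f = 0.25, t = 0.50: (1 − 0.15)/(1 − 0.075) = 0.85/0.925 = 0.92. The correction makes the pathway look better.
- f = 0.50, t = 0.25: (1 − 0.075)/(1 − 0.15) = 0.925/0.85 = 1.09. The correction makes it look worse.

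The sign depends on whether t exceeds f, and the documents give neither.

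**The case against.** The assumption is openly labelled as one, the article condenses a longer plan, and the full economic model may contain a self-presentation branch. Late presenters may also gain little, and no baseline attendance data exist. The primary outcome and the sample size are untouched.

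Much of this is fair, but it does not remove the point. The untreated course is stated outright, without adjustment, so this is not an omission that a fuller document would be expected to fill. Late presentation lowers f without making it zero, and the protocol says that some patients come through awareness rather than loss of vision. Not knowing s is a reason to vary it, not to fix it at zero.

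Several stronger readings are tempting, and the documents do not support them:
- *Most STDR patients are already treated.* The sentence on voluntary presentation can describe the route taken by those who do present. It gives no share of STDR patients who present or are treated.
- *The overstatement is 1/(1 − s).* That sets f = 1, so that later treatment works as well as screening-led treatment. It is the extreme case for any given s.
- *Cost per QALY is biased in the pathway's favour.* The Sample size section puts STDR at 3% and referral at about 20%. That means roughly 1/0.03 = 33 people screened and 0.20/0.03 = 7 referred per STDR case, costs that self-presentation does not bear. A low t is therefore plausible, but it is not established. Omission of current-care costs is itself inferred, not stated.
- *The planned data will supply s.* Counts of presenters and an analysis of self-referred patients give case-mix. They lack the denominator of all STDR patients.
- *The cataract QALYs share the fault.* The quoted assumption concerns STDR only, and no cataract comparator is stated.

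**Conclusion.** The point holds for effects. By the protocol's own description, care without screening includes self-presentation and management, so an untreated comparator overstates blindness averted and STDR QALYs whenever s and f are both above zero. This rests on management at the tertiary centre having some benefit; the documents say that cases are managed there but give no treatment rate or effect.

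The size cannot be fixed from the documents. Illustrative factors run from about 1.03 to 2.0, and they are not estimates. No conclusion is drawn on the net direction for cost per QALY, or on the cataract component. The change should be made before the economic results feed the scale-up plan.

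**What to change.** - Make current practice the base-case comparator, with a self-presentation branch that carries both the effect and the cost of treatment.
- Take severity and visual acuity at presentation from the planned tertiary-centre and self-referral data.
- Take s and f from the literature or expert opinion, which Table 2 already allows, and vary both over a wide range.
- Apply the untreated course only to patients who never present.
- Report the fully untreated comparator as an upper bound on blindness averted.

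The cost is a little more modelling, an assumed input for s, and a smaller stated benefit. Cost per QALY may move either way.
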